## Abstract

**Background:**

Topiramate might be effective in the treatment of posttraumatic stress disorder (PTSD) because of its antikindling effect and its action in both inhibitory and excitatory neurotransmitters. Open-label studies and few controlled trials have suggested that this anticonvulsant may have therapeutic potential in PTSD. This 12-week randomized, double-blind, placebo-controlled clinical trial will compare the efficacy of topiramate with placebo and study the tolerability of topiramate in the treatment of PTSD.

**Methods and design:**

Seventy-two adult outpatients with DSM-IV-diagnosed PTSD will be recruited from the violence program of Federal University of São Paulo Hospital (UNIFESP). After informed consent, screening, and a one week period of wash out, subjects will be randomized to either placebo or topiramate for 12 weeks. The primary efficacy endpoint will be the change in the Clinician-administered PTSD scale (CAPS) total score from baseline to the final visit at 12 weeks.

**Discussion:**

The development of treatments for PTSD is challenging due to the complexity of the symptoms and psychiatric comorbidities. The selective serotonin reuptake inhibitors (SSRIs) are the mainstream treatment for PTSD, but many patients do not have a satisfactory response to antidepressants. Although there are limited clinical studies available to assess the efficacy of topiramate for PTSD, the findings of prior trials suggest this anticonvulsant may be promising in the management of these patients.

**Trial Registration:**

NCT 00725920

## Background

Posttraumatic stress disorder (PTSD) is the only psychiatric disorder that has an etiologic component: exposure to a traumatic event. The disorder is characterized by three symptom clusters: reexperience of the event, avoidance/numbing, and hyperarousal resulting from exposure to a traumatic event[1]. Data from the National Comorbidity Survey in United States estimated a lifetime PTSD prevalence rate at 7.8% (10.4% for women and 5% for men) and to be more prevalent among women and the previously married. The trauma most likely to be associated with development of PTSD among men (69%) and women (45.9%) alike was rape. Survival analyses demonstrated that PTSD failed to remit in more than one third of persons even after several years of the occurrence of the traumatic event, demonstrating that PTSD tends to be a chronic disorder [2].

Furthermore, PTSD has a high comorbidity with other psychiatric conditions such as substance abuse/dependence, anxiety disorders, and major depressive disorder causing a worsening prognosis [2].

The development of treatments for PTSD is challenging due to the complexity of the symptoms and psychiatric comorbidities. Psychotherapy and pharmacotherapy are the two main classes of PTSD treatment. In the Cochrane systematic review, Bisson and Andrew [3] evaluated the efficacy of five categories of psychotherapeutic interventions: trauma-focused cognitive- behavioral therapy/exposure therapy (TFCBT), stress management, other therapies (supportive therapy, nondirective counseling, psychodynamic therapy, and hypnotherapy), group cognitive behavioral therapy and eye movement desensitization and reprocessing (EMDR). The authors analysed thirty-three studies and concluded that individual TFCBT, stress management, group TFCBT, and EMDR were more effective than wait list and other therapies. Bradley et al [4] conducted a multidimensional meta-analysis of psychotherapy studies published between 1980 and 2003. The meta-analysis included twenty six studies and reviewed exposure therapy, cognitive behavioral therapy (CBT), exposure plus CBT, EMDR and others. The authors found that exposure therapies, other cognitive behavior therapy approaches, and EMDR are efficacious in reducing PTSD, but found no significant differences between the various CBT modalities and between CBT and EMDR. Several review of psychotherapy have been published demonstrating that cognitive-behavioural and similar psychotherapies are effective in the treatment of PTSD.

The National Institute for Clinical Excellence (NICE) [5] recommended trauma focused psychological therapy as a routine first-line treatment for adults in preference to pharmacotherapy. In cases that drug treatment is required, paroxetine and mirtazapine were approved for general use, and amitriptyline and phenelzine for use only by mental health specialists. Although controlled trials with paroxetine did not show significant benefits on the main outcome variables, this is the only drug approved for PTSD in UK.

In a recently published systematic review, Stein et al [6] evaluated thirty five short term randomized controlled medication trials for PTSD (4597 participants). In thirteen trials, response to medication occurred in 59.1% of patients (644 participants), while response to placebo was seen in 38.5% of patients (628 participants). Significant reductions in symptom severity were observed for patients who received medications in seventeen trials. The mean total CAPS score for the medication group was 5.76 points lower than that for the placebo group (95% CI – 8.16 to -3.36 and 2507 participants). Evidence of treatment efficacy was most convincing for the SSRIs. Furthermore, medication was superior to placebo in reducing the severity of the three symptom clusters of PTSD, as well as alleviating the symptoms of depression, and in improving the quality of life measures. The current evidence base of randomized clinical trials is unable to demonstrate superior efficacy or acceptability for any particular medication class.

Nevertheless, the bulk of evidence for the efficacy of medication has been with the SSRIs and supports expert consensus guidelines that these medications constitute the first-line medication choice in PTSD.

The American Psychiatric Association [7] practice guidelines rated the SSRIs as first-line pharmacotherapy, with sertraline and paroxetine being US Food and Drug Administration approved for PTSD. The authors did not find efficacious pharmacological intervention to recommend in preventing the development of acute stress disorder or PTSD. The tricyclics antidepressants and monoamine oxidase inhibitors may also be beneficial (recommended with moderate clinical confidence) and the benzodiazepines, anticonvulsants, antipsychotics and adrenergic inhibitors may be recommended on the basis of individual circumstances. Trials of atypical antipsychotics olanzapine and risperidone found some evidence in terms of efficacy for PTSD with psychotic symptoms. Olanzapine, a second-generation antipsychotic agent, when prescribed to augment ongoing sertraline treatment, was shown to produce improvement in PTSD, depressive, and sleep-related symptoms in Vietnam veterans [8]. Open-label studies of adjunctive olanzapine have demonstrated symptom reduction in veterans with PTSD [9]. A small controlled study of risperidone in chronic combat related PTSD and comorbid psychotic symptoms demonstrated that reexperiencing and global psychotic symptoms were reduced [10]. Although the SSRIs are the mainstream treatment for PTSD, many patients do not have a satisfactory response to these antidepressants. The development of pharmacological treatments for PTSD is challenging due to the heterogeneity of symptoms. Recently, anticonvulsants have been evaluated for their potential efficacy for the treatment of PTSD. Open and randomized trials of carbamazepine [11], valproic acid [12,13], and lamotrigine [14] suggested that these agents may be efficacious in PTSD treatment.

The hypotheses on the etiology of PTSD have suggested that after exposure to traumatic events; the limbic nuclei may become kindled or sensitized, resulting in increased susceptibility to physiologic arousal [15,16]. The implication of the limbic kindling-like phenomenon in the pathophysiology of PTSD has stimulated clinical research in antiepileptic drugs in the treatment of PTSD.

Topiramate is an anticonvulsant with inhibitory activity in animal kindling models and with multiple mechanisms of action: inhibition of carbonic anhydrase, blockade of Na+ channels, inhibition of some high-voltage-activated Ca2+, negative modulating effect on the kainate/AMPA (α-amino-3-hydroxy-5-methylisoxazole-4-proprionic acid) subtype of glutamate receptors, ability to modulate NMDA (Nmethyl-D-aspartate) glutamate receptor and enhancement of GABAergic activity at GABA2 receptors [17,18].

The blockage or the stabilization of the AMPA (α-amino-3-hydroxy-5 methyl-4 isoxazole propionic acid) receptor may be a possible mechanism responsible for the increase in the threshold for flashbacks and nightmares that may explain the treatment response to topiramate in PTSD [19]. Several animal model studies show that AMPA antagonists attenuate acoustic startle response when administered into the amygdala. For instance, Khan and Liberzon [20] demonstrated that topiramate reduced significantly the acoustic startle response in rats after a single prolonged stress episode.

Glutamatergic neurons play a role in the neuronal plasticity associated with longterm potentiating in adaptation to stress [21]. Glutamate is the primary excitatory neurotransmitter in the central nervous system. Glutamate NMDA (N-methyl D-aspartate) receptors have been implicated in reconsolidation, and extinction of memories. The reconsolidation of spatial and contextual fear memory and odor reward association is impaired by NMDA antagonists [22,23]. Lee et al [24] demonstrated that the NMDA receptor antagonist (+)-5-methyl-10,11-dihydro-SHdibenzo [a, d] cyclohepten-5,10-imine maleate (MK-801) blocked and the agonist D-cycloserine (DCS) potentiated extinction of fear memory when they were administered before a long extinction training session whereas MK-801 impaired and DCS increased reconsolidation of memory when they were administered before brief memory reactivation session.

Although much of the research associate the glutamatergic systems with learning and memory; the GABAergic (γ-aminobutyric acid) system in the basolateral amygdala, is also involved in the acquisition and extinction of fear memories [25]. Reduced GABA function is involved in the formation of fear memories and the development of anxiety disorder. Stork et al [26] found that conditioned fear in mice is associated with a reduction of extracellular GABA levels in the amygdala indicative of a reduced GABA release and/or increased GABA uptake from the extracellular space.

Clinical studies with topiramate suggest that it is effective as monotherapy or adjunctive therapy in PTSD. Two open-label studies demonstrated topiramate to be effective and to have a rapid onset of action. Berlant and van Kammen [27] have reported that topiramate decreased nightmares in 79% and flashbacks in 86% of civilian patients with chronic PTSD with improvement of nightmares in 50% and of intrusions in 54% of patients with these symptoms. A partial response was reported for 95% of patients at a dosage of 75 mg/day or less and in 91% of full responders at a dosage of 100 mg/day or less. The nonhallucinatory subgroup achieved a higher response rate (89%). In a prospective open-label study, Berlant [28] treated thirty three civilians with chronic PTSD, with topiramate as monotherapy or augmentation therapy. The PTSD Checklist-Civilian Version (PCL-C) total symptoms declined by 49% at 4th week, with similar subscale reductions for reexperiencing, avoidance/numbing, and hyperarousal symptoms. Topiramate suppressed nightmares in 79% and decreased symptoms of intrusions in 94% in those patients with these symptoms. There is only one double-blind, placebo- controlled study of topiramate as a monotherapy in PTSD. Tucker [29] conducted a 12-week, double-blind, placebo-controlled evaluation of topiramate as a monotherapy in thirty eight civilian PTSD patients. Patients in the topiramate group exhibited significant reductions in reexperiencing symptoms (CAPS cluster B: topiramate = 74.9%; placebo = 50.2%; p = .038) and reductions approaching statistical significance, based on a nominal p value, were noted in mean total Clinical Global Impressions-Improvement Scale scores (topiramate = 1.9 ± 1.2; placebo = 2.6 ± 1.1; p = .055). Although there was a reduction in total Clinician-Administered PTSD Scale (CAPS) score from baseline (topiramate = -52.7; placebo = -42.0), the difference was not statistically significant (p = .232). But not all studies found positive results, Lindley [30] in a double-blind, placebo-controlled study using topiramate as an augmentation therapy in forty male veterans with PTSD did not find significant treatment effects versus placebo. However, there was a high dropout rate from the study with 11 (55%) topiramate and 5 (25%) placebo subjects not completing the seven week treatment, with 40% of topiramate and 10% of placebo dropping because of adverse effects. Patients in the topiramate group that completed the study, had a significant improvement in the reexperiencing subscale of the CAPS suggesting efficacy for the patients that continued the medication.

Extensive efforts have been made to establish guidelines based in evidence for PTSD treatment, however there is still no specific drug proved efficacious. Although there are limited clinical studies with topiramate in the treatment of PTSD, the findings of prior topiramate studies suggest that this anticonvulsant may be promising in the management of patients with PTSD.

### Aims of the Study

1) To compare the efficacy of topiramate with placebo in the treatment of PTSD. Clinical response will be considered when there are a 20% reduction on CAPS scale scores from baseline and remission when CAPS score is less than 19.

2) To study the tolerability of topiramate in the treatment of PTSD, through the dropout rate in each group.

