### Research Goals

The trial will compare the efficacy of topiramate with placebo in the treatment of PTSD, and will study its tolerability through the drop out rate in each group. The primary hypothesis is that topiramate will be superior to placebo in the treatment of PTSD. Secondary research goals includes studying the efficacy of topiramate in social adjustment, functioning and quality of life. Additionally, evaluating treatment adhesion, and studying the efficacy of topiramate in depressive symptoms.

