#### Active treatment phase

Those patients without improvement during the placebo trial, and do not show any laboratory and clinical condition exclusion criteria will be randomly assigned to receive either placebo or topiramate, in a 1:1 ratio using computer- generated code. The active and placebo pills will be identical. All research and clinical staff will be blinded to the randomized assignments.

Study medication will start at 25 mg/day once daily, at night, and will be increased 25 mg weekly, as tolerated, until complete or nearly complete efficacy is achieved or until 200 mg/day is reached. No other psychotropic medications will be allowed during the study, except for zolpidem (10 mg/day), if needed, for insomnia.

Study follow-up visits will be conducted at baseline, and weeks 1, 2, 3, 4, 6, 8, and 12.

Symptoms and side effects will be assessed, as well as measurement of systemic blood pressure and pulse rate in each visit by the investigator, who is blind to medication assignment. Compliance will be assessed by counting the amount of pills left in the bottle of medicine in each visit.

Treatment will be continued for 12 weeks (active treatment phase); then drug administration will be withdrawn gradually during 2 weeks with reductions of 25/50 mg every three days, according to the final dosage reached.

Patients will be assessed until completing 6 months during a follow-up period. If a patient showed a symptomatology worsening during the active treatment phase (12 weeks) when receiving active drug treatment, characterized by a one-point decrease at CGI -I or present serious adverse effects related to medication, he/she will be excluded from the study.

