Efficacy analyses will be performed in the intent-to-treat population of patients who received at least one dose of topiramate. The primary efficacy endpoint will be the change in PTSD Scale- CAPS total score from baseline to the final visit at 12 weeks, which will be compared between treatment groups. Missing efficacy data at 12 weeks will be imputed with the last observation carried forward. The secondary outcomes between groups will be comparing the Clinical Global Impressions (CGI), the Beck Depression Inventory (BDI), the Global Assessment of Function (GAF), and the PANAS scales. Other secondary analyses will include an evaluation after 24-weeks (12-week after last patient visit with drug) data with endpoint analyses between the treatment groups covarying for baseline scores. On all secondary outcomes, the Bonferroni correction will be applied for testing multiple variables. Response will be defined as a 20% improvement in the baseline CAPS total or positive symptom scores at 12 weeks and will be compared between treatment groups using a chi-square test. Proportions of patients completing the 12-week double-blind study will be compared between treatment groups using a chi-square test. Adverse events reported by 10% of patients in each treatment group will be compared using a chi-square test. Laboratory values, vital signs and physical examinations are going to be compared from baseline and in reference to normal ranges, and reported as normal or abnormal. Changes in body weight (lb), body mass index (BMI; kg/m2) at last visit in the 12-week dataset will be compared as mean changes between treatment groups using t-tests.

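### Tolerability, the second aim, is measured by dropout from any cause, which mixes lack of efficacy with intolerance and can bias the conclusion in either direction

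*Protocol article*

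**What the plan says.** The Aims section gives as its second aim "To study the tolerability of topiramate in the treatment of PTSD, through the dropout rate in each group". The Research Goals section repeats that the trial "will study its tolerability through the drop out rate in each group". Neither limits dropout to any cause.

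The matching test is in the Statistical Analysis section: "Proportions of patients completing the 12-week double-blind study will be compared between treatment groups using a chi-square test".

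The Active treatment phase section sets out who is taken out of the trial. One sentence covers two grounds. The first is efficacy failure: "If a patient showed a symptomatology worsening during the active treatment phase (12 weeks) when receiving active drug treatment". The second is intolerance: such a patient may "present serious adverse effects related to medication, he/she will be excluded from the study".

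The Statistical Analysis section also plans other safety comparisons: "Adverse events reported by 10% of patients in each treatment group will be compared using a chi-square test". It adds laboratory values, vital signs, physical examinations and change in weight and BMI. Side effects are assessed at each visit.

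The Background separates the two kinds of dropout when it describes the earlier augmentation trial. It gives 11 (55%) v 5 (25%) not completing, "with 40% of topiramate and 10% of placebo dropping because of adverse effects".

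**The concern.** Tolerability asks how many patients could not stay on the drug because of its effects on them. All-cause dropout asks how many did not stay for any reason. That is usually called acceptability, and it depends on efficacy as well as on side effects.

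The two differ here because the protocol's own withdrawal rule sends patients with worsening symptoms into the same count as patients with serious adverse effects. The primary hypothesis is that topiramate works. If it does, exits for lack of effect may be more frequent on placebo and would offset an excess of adverse-effect exits on topiramate.

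The bias could also run the other way. The worsening rule is worded for patients receiving active drug. If it were applied in that arm only, efficacy withdrawals would count against topiramate and make it look less tolerable than it is.

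At stake is the reading of the second aim, not the primary CAPS result.

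**Working it through.** **The plan's own figure.** The protocol gives no expected dropout rate or power for this aim, so there is nothing of its own to reproduce on this point. Its sample size rests on response (60% v 30%), and only the 36 per arm is used below. The standard two-sided pooled formula gives 42 per arm for those response rates. That is a separate matter and does not affect what follows.

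**Inputs.** From the Background, for the cited augmentation trial of 40 patients:
- 11 is 55% and 5 is 25%, so there were 20 patients per arm.
- Adverse-effect dropout: 40% of 20 = 8 on topiramate; 10% of 20 = 2 on placebo.
- Other-cause dropout, taking one reason per patient: 11 − 8 = 3 (15%) and 5 − 2 = 3 (15%).

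**Step 1: the two measures in the cited trial.** Uncorrected chi-square = N(ad − bc)² / (product of the four margins).
- All-cause: 40 × (11×15 − 9×5)² / (20×20×16×24) = 3.75, p = .053 (Fisher .105). Risk difference 30 points; risk ratio 55/25 = 2.2.
- Adverse-effect: 40 × (8×18 − 12×2)² / (20×20×10×30) = 4.80, p = .028 (Fisher .065). Risk difference 30 points; risk ratio 40/10 = 4.0.

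With 15% other-cause dropout in each arm, mixing leaves the difference unchanged. It lowers the ratio and adds variance.

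**Step 2: power at 36 per arm with those rates.** Power ≈ Φ{[√n·|p₁ − p₂| − 1.96·√(2p̄(1 − p̄))] / √(p₁(1 − p₁) + p₂(1 − p₂))}.
- 55% v 25%: (1.800 − 1.358) / 0.660 = 0.670, giving 75% (exact enumeration of the chi-square test 75%).
- 40% v 10%: (1.800 − 1.200) / 0.574 = 1.044, giving 85% (exact 86%).

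**Step 3: unequal other-cause dropout (assumption).** Adverse-effect dropout stays at 40% v 10% and other-cause dropout on topiramate at 15%. Other-cause dropout on placebo is varied. Power is by exact enumeration.

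| Other-cause dropout, placebo | All-cause dropout | Power, all-cause | Power, adverse-effect |
|---|---|---|---|
| 15% (as cited) | 55% v 25% | 75% | 86% |
| 20% | 55% v 30% | 57% | 86% |
| 25% | 55% v 35% | 39% | 86% |
| 30% | 55% v 40% | 23% | 86% |
| 35% | 55% v 45% | 13% | 86% |
| 40% | 55% v 50% | 7% | 86% |
| 45% | 55% v 55% | 5% | 86% |

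**Step 4: the opposite direction (assumption).** Suppose adverse-effect dropout were equal at 10% and other-cause dropout were 45% on topiramate and 15% on placebo. All-cause dropout would be 10 + 45 = 55% v 10 + 15 = 25%, the same as in the cited trial. The stated measure would then have the same 75% chance of showing a difference, although adverse-effect dropout did not differ. All-cause dropout cannot tell the two situations apart.

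**The case against.** The best case for the plan has five parts.

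- **Tolerability is examined elsewhere.** Side effects are assessed at every visit, and common adverse events, laboratory values, vital signs and weight are compared or reported. An excess of adverse effects on topiramate could show there. This stands, and it limits the harm. But none of these analyses is tied to the second aim, and event frequencies do not show who stopped because of them.
- **The documents' only data show no masking.** This also stands. A reader might infer that all-cause dropout will hide poor tolerability, or that the second aim will go unanswered. The cited figures do not support that: other-cause dropout was 15% in each arm, and both measures gave the same 30-point difference. Hiding needs clearly more other-cause dropout on placebo, which has to be assumed. For example, adverse-event dropout of 20% v 5% with other dropout of 5% v 20% gives 25% v 25% and 5% power, but those rates are chosen to cancel exactly. Even there the adverse-event comparison has only 53% power.
- **The p-values on either side of .05 prove little.** Agreed. By Fisher's test both are above .05 (.105 and .065).
- **Dropout by reason is commonly left to the full protocol or case report form.** True of the tabulation, and nothing says that reasons go unrecorded. The point is that the article positively names unrestricted dropout as the tolerability measure.
- **All-cause dropout needs no attribution of cause.** This is a real advantage and a reason to keep it, under a name that fits what it measures.

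**Conclusion.** The point holds as a flaw of moderate weight in how the second aim is measured. The protocol defines tolerability through dropout of any cause while withdrawing patients for worsening as well as for serious adverse effects, so the measure mixes efficacy with tolerability.

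What the documents' own figures support is dilution: a risk ratio of 2.2 instead of 4.0 and power of 75% instead of 86% at 36 per arm. Those figures come from a small augmentation trial in male veterans that found no significant treatment effect versus placebo. Its equal other-cause dropout therefore says little about a monotherapy trial planned on 60% v 30% response.

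A larger loss, to about 39% or 23% power, rests on the assumption of 25% or 30% other-cause dropout on placebo against 15% on topiramate. The direction of any bias is uncertain. It depends on how effective the drug is and on whether the worsening rule is applied in both arms. The safety comparisons mitigate the problem in part.

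**What to change.** - Make discontinuation because of adverse events the tolerability measure for the second aim. Compare it between arms with a risk difference and 95% CI, using Fisher's test where cells are small, as the plan already does for the CAPS severity tables.
- Assign one primary reason to every discontinuation while allocation is still blind, with worsening and adverse effects as separate categories.
- Keep the planned comparison of completion, labelled as acceptability.
- Read both results alongside the planned adverse-event comparisons.

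The cost is one reason-for-discontinuation field, if the case report form does not already have one, and one further 2 × 2 comparison. Visits and sample size are unaffected. The small downside is that attributing a reason involves judgement; doing so blind and keeping the all-cause result beside it limits this.
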